# Online self-compassion training to improve the wellbeing of youth with chronic medical conditions: protocol for a randomised control trial

**DOI:** 10.1186/s12889-020-8226-7

**Published:** 2020-01-28

**Keywords:** Chronic illness, Chronic medical conditions, Youth, Self-compassion, Online, Digital health

## Abstract

**Background:**

Chronic medical conditions (CMCs) affect up to 35% of children and adolescents. Youth with chronic medical conditions are at an increased risk of psychological distress and reduced health-related quality of life, and report rates of mental illness up to double that of their physically healthy peers. Accessible, evidence-based interventions for young people with chronic illness are urgently required to improve their mental health and daily functioning. Self-compassion involves taking a mindful, accepting approach to difficult experiences, being aware that one is not alone in one’s suffering, and being kind and understanding with oneself during challenging times. Self-compassion shares strong associations with mental health outcomes among young people and preliminary work indicates that interventions that build self-compassion have the potential to substantially improve youth mental health. Self-compassion is also associated with better physical and mental health outcomes among individuals living with CMCs. While face-to-face self-compassion training is available, there are several barriers to access for youth with CMCs. Online self-compassion training potentially offers an accessible alternative for this high-risk group.

**Methods:**

Self-Compassion Online (SCO) is a self-compassion program that has been tested with a non-clinical adult group. For the proposed trial, a reference group of youth (16–25 years) with chronic illness reviewed the program and proposed adaptations to improve its suitability for youth with chronic illness. In alignment with the SPIRIT Checklist, this paper outlines the protocol for a CONSORT-compliant, single-blind randomised controlled trial to test the efficacy of the adapted program, relative to a waitlist control, for improving self-compassion, wellbeing, distress, emotion regulation, coping and quality of life among young Australians with CMCs. Mechanisms of action and feasibility of SCO will be analysed using quantitative data and participant interviews, respectively. Finally, cost-utility will be analysed using health-related quality of life data.

**Discussion:**

The SCO program could provide a scalable solution for improving psychological outcomes and quality of life among youth with chronic illness. The proposed trial will be the first to determine its efficacy for improving these outcomes, relative to waitlist control.

**Trial registration:**

The trial was registered on the Australian New Zealand Clinical Trials Registry on the 11th April 2019, ACTRN12619000572167.

**Protocol version:** Version 2, 21 December 2019.

## Background

Chronic medical conditions (CMCs) are those that last longer than 6 months and are likely to require medical follow up for more than a year [47]. Included under this umbrella are conditions such as diabetes, asthma, arthritis, and cancer. Prevalence of CMCs among children and adolescents is increasing and, depending on which conditions are included, prevalence estimates of CMCs in children and adolescents ranges from approximately 10–30% [25, 63, 65]. Estimates from population-based studies in the United States have found that over 30% of adolescents report one or more chronic conditions [46, 59]. In addition to placing substantial burden on the healthcare system, CMCs can carry substantial impacts for affected young people and their families. For example, young people with CMCs face many significant impacts on daily functioning, including pain, fatigue, and problems with sleeping patterns, social functioning, family relationships, school and occupational performance [53].

Youth with CMCs are also at substantially increased risk of mental illness [16], with population-based studies indicating that children with at least one chronic physical condition are 62% more likely to have a mental illness than those without chronic physical conditions [58]. A recent study found that 35.3% of young people in the general population have experienced co-occurring mental and physical disorders [59]. Findings from studies with adults also consistently demonstrate the co-occurrence of mental and physical disorders [15] and highlight the impact of such comorbidities on quality of life [5], disease management, and cost of care [66]. Such findings demonstrate the need to support psychological wellbeing among individuals with CMCs, particularly during adolescence and young adulthood, when individuals undergo multiple transitions [3] and experience heightened vulnerability to psychological distress [54].

Systematic reviews of psychological interventions for adolescents and young adults living with CMCs repeatedly highlight the need for accessible and age-appropriate interventions to address distress and promote wellbeing [51, 52]. Low uptake of existing interventions suggests the need for engaging alternatives that are theoretically sound. Self-compassion-based interventions are one such alternative. Self-compassion is associated with a range of advantageous mental health outcomes among young people [42], and emerging evidence indicates that interventions that build self-compassion have the potential to substantially improve youth mental health [8, 9]. Furthermore, several studies have shown an associated between self-compassion and better outcomes in adults with CMCs [26, 55, 56]. The current paper describes the protocol for a randomised controlled trial of online self-compassion training to promote wellbeing and reduce distress among young Australians with CMCs.

### Intervention approach and theoretical basis

The self-compassion intervention is based on the self-regulation model of chronic illness proposed by Lansing and Berg [38], which highlights the role of cognitive, affective and behavioural regulation in supporting resilience in the face of CMCs. Young people with CMCs are frequently required to deploy self-regulatory resources in order to maintain goal-directed behaviour, such as adhering to treatment regimens in the face of challenges or setbacks (for example, pain, fatigue, and social isolation [38];). Problematic emotion regulation and the use of maladaptive coping strategies are key drivers of maladjustment and negative psychological outcomes among patients with CMCs [13]. For example, emotion regulation strategies predict pain and functioning in youth with arthritis [14], and maladaptive coping strategies such as self-blame and rumination predict depressive symptoms in adolescents with diabetes [37]. As a result, interventions that promote self-regulation and teach adaptive coping skills have been identified as a priority for young people with CMCs [52].

Self-compassion is a parsimonious construct for supporting self-regulation across cognitive, emotional and behavioural domains, particularly in the context of chronic illness [55, 56] and psychiatric vulnerability [23]. Self-compassion is an adaptive form of relating to oneself in times of difficulty that involves three interconnected capacities: the ability to notice when one is struggling and to respond to difficult experiences in a balanced way; an appreciation of the “common humanity” inherent in challenges and awareness that one is not alone in one’s struggles; and the capacity to be kind and understanding with oneself during times of difficulty [45]. Self-compassion is a transdiagnostic resilience variable that promotes adaptive psychological and physiological self-regulatory responses to stress [2, 9, 20], and has been found to buffer the impact of stressful experiences on adolescent and young adult mental health, including traumatic events [68] and victimization [33, 34]. A recent meta-analysis found a large effect size for the inverse relationship between self-compassion and psychological distress across 19 studies of youth aged 10–19 [42].

Self-compassion is associated with less psychopathology and greater quality of life across multiple chronic illness groups, including among patients with cancer [49], HIV [10], epilepsy [12], inflammatory bowel disease (IBD), and arthritis [55, 56]. By promoting adaptive emotion regulation in the face of difficult experiences [23], self-compassion may support individuals to cope with the experience of chronic illness, as well as buffering the detrimental impact of self-stigma [29]. This has been demonstrated in a study of patients with IBD and arthritis, where self-compassion was found to predict adaptive coping, which in turn was associated with enhanced coping efficacy and reductions in perceived stress [55, 56]. Additionally, self-compassion may play a role in quality of life in individuals with CMCs as it is associated with increased engagement in health-promoting behaviours [57].

Previous studies of self-compassion training for adults with CMCs have demonstrated positive effects on mental and physical health outcomes. For example, a randomised controlled trial comparing self-compassion training with waitlist control for adults with diabetes found significant improvements in mental health and metabolic outcomes among the intervention group [26]. In addition, a randomised controlled trial of self-compassion training compared with an active control (relaxation) reported a 40% absolute risk reduction for health status in the intervention group for patients with fibromyalgia [43]. Further, previous work has found that self-compassion interventions improve mental health and wellbeing among healthy adolescents [8, 9, 28]. However, in each of these studies, the intervention has been delivered as a face-to-face, group-based intervention (approximately 2 h per week for 6–8 weeks). Arguably, this mode of delivery is not well-suited to many adolescents and young adults with CMCs, who may experience limitations in their capacity to access face-to-face services, as well as already bearing a high time and resource burden for medical treatment. Digital health interventions are an efficacious alternative to face-to-face care for youth mental health [48], although there is currently only low-quality evidence to support their use among young people with CMCs [60]. The current trial will examine a brief, online self-compassion training program to improve psychological wellbeing among young people with CMCs. Using a randomized design with a wait-list control, we will provide evidence regarding efficacy, acceptability, and cost-utility. A waitlist control was considered appropriate given that this and exploratory study and we are also interested in testing the feasibility and acceptability of the intervention with the target group. The waitlist control group will access treatment as usual.

Self-Compassion Online (SCO) is a self-guided web-based program grounded in an emotion regulation model of self-compassion [24]. The program draws on key elements of the mindfulness and acceptance-based model of therapeutic change, including psychoeducation, meditation, and self-reflective exercises [24]. The SCO program has been piloted with a non-clinical, primarily young adult sample, who reported significant pre-post improvements in depression, stress, emotion regulation, happiness, and self-compassion [24]. Feedback from the pilot of the program led to revisions in terms of length (from six to 4 weeks) and complexity of content. For the purposes of the current trial, the program was further adapted to make it appropriate for adolescents and to ensure relevance and application to the challenges of living with a CMC. The adapted program was reviewed by members of a Youth Reference Group (YRG) consisting of eight young people (16–25 years) living with a CMC. The YRG provided feedback about each of the four modules in the program, via a combination of online surveys and online consultations. Two online consultations were held; one in which initial feedback was sought, and a second, in which the adaptations made were discussed to ensure alignment with feedback. Based on this feedback, the SCO content and structure were further refined prior to the current trial. An overview of the revised intervention – Self-Compassion Online – Chronic Medical Conditions (SCO-CMC) is shown in Table 1.

**Table 1 Tab1:** Self-compassion Online Program Overview

Module	Content
Befriending Yourself	Introduction to self-compassion Understanding the inner critic Understanding relationships between thoughts, feelings, and behaviours Being a friend to yourself
Calming Your Mind	Three affect regulation systems Anchoring your mind Training your attention (breath-focused meditation) Alternative anchors (five senses practice) Coping with difficult feelings
Understanding your Strengths	Understanding character strengths Using your strengths Self-acceptance Connecting with others Loving Kindness Practice
Cultivating a Meaningful Life	Appreciating the good Identifying your values Using your values Values and self-compassion Moving forward

### Aims and hypotheses

The primary aim of this trial is to determine whether SCO-CMC can produce significant improvements in self-compassion, emotion regulation and coping, relative to a waitlist control, among youth with CMCs (16–25 years). In addition, we will investigate whether the intervention is associated with improvements in psychological distress, wellbeing, and quality of life and whether improvements in self-compassion, emotion regulation and coping mediate the effect of the intervention on wellbeing, distress and quality of life. A secondary aim of the study is to determine the cost-utility of the program by calculating the incremental cost-utility ratio for the intervention compared to usual care. Finally, we also aim to examine feasibility of the program, by examining enrolment and retention rates, and determine satisfaction and acceptability of the program by interviewing young people who took part.

It is hypothesized that relative to waitlist control, the SCO-CMC group will:
Report significant increases in self-compassion and approach coping, and significant decreases in emotion regulation difficulties and avoidant copingReport significant reductions in symptoms of psychological distressReport significant improvements in quality of life and wellbeing

It is also expected that improvements in self-compassion, emotion regulation, and coping will mediate the relationship between treatment group and reduced psychological distress, as well as improved wellbeing and QoL.

## Methods/design

### Ethics approval

The study protocol was approved by the Human Research Ethics Committee at Curtin University HRE2019–0386.

### Trial design and study setting

The proposed study is an exploratory single-blind CONSORT-compliant randomised controlled trial, comparing online self-compassion training (SCO-CMC) with a waitlist control group (WLC). The intervention and data collection will be online, with data collected from Australian residents only.

### Participants

Participants will be *N* = 96 Australian adolescents and young adults (48 per group), aged between 16 and 25 years, who self-report a current diagnosis of a CMC (for example arthritis, asthma, cancer, cystic fibrosis, diabetes, epilepsy, haemophilia, IBD, lupus, multiple sclerosis, and myalgic encephalomyelitis). Additional inclusion criteria are as follows (1) Australian resident; (2) fluent English speaker; (3) regular access to the Internet; (4) able to access online video and audio content.

### Sample size

Using medium effect sizes, 40 participants per group are required for power = .80 and α = .05 [21]. To allow for typical treatment drop out of approximately ~ 15–20% [17] a target of 48 people per group has been set. This sample size is also sufficient to detect a medium effect for the purposes of the mediation analysis [27].

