### Statistical analysis

#### Tests of intervention effects

We will perform Intention to Treat and Per Protocol analyses, conduct a sensitivity analysis [39], and compare complete cases versus cases lost to follow-up on baseline characteristics and scores on clinical measures, by randomisation group [64]. GLMM Mixed Model Repeated Measures will compare change in outcome measures across conditions, and time points, while controlling for random effects including age and gender. The group*time interaction will be calculated as a test of intervention effects. Using DASS-21 scores participants will be classified into outcome categories (Recovered, Improved, Unchanged, Deteriorated) according to Reliable Change Index and Clinical Significance of change at post-treatment and follow-up [32], to determine whether the SCO-CMC and control groups differ in clinically significant treatment outcome over time (Cochrane’s Q).

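### The stated 80% power at 40 per group does not follow from the inputs given: it holds for the planned test only at an unstated within-person correlation of about 0.66 or more, and 48 per group falls slightly short at 20% loss

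*Protocol article*

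**What the plan says.** The Sample size section opens "Using medium effect sizes" and states that "40 participants per group are required for power" of .80 at α = .05. It then allows for "typical treatment drop out of approximately ~ 15–20" per cent, on which basis "a target of 48 people per group has been set", giving N = 96. An outside source is cited for the power figure. The section does not say which effect metric is meant, which outcome or contrast the power refers to, whether the test is one- or two-sided, or what correlation between repeated measures was assumed.

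Elsewhere the article fixes the analysis. Under Tests of intervention effects a repeated-measures mixed model is planned and "The group*time interaction will be calculated as a test of intervention effects". Under Recruitment, randomisation and allocation there are three assessments: baseline, week 4 and week 12. Under Aims and hypotheses the primary aim concerns "significant improvements in self-compassion, emotion regulation and coping", with coping split into approach and avoidant coping in the first hypothesis.

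**The concern.** In a two-arm trial the plain reading of a medium effect is a standardised mean difference of 0.5. For a simple two-group comparison that needs well over 40 per group, so the sentence fails on its face. The analysis actually planned is different, and its power depends heavily on a correlation that the article does not give. A reader therefore cannot tell what size of effect the trial is built to detect.

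What is at stake is how a null result is read. If .80 power for a medium effect is taken at face value, a non-significant interaction could be reported as making a medium effect unlikely. Depending on the correlation, the same sample may or may not support that statement. The dropout allowance raises a smaller question of the same kind: whether the number recruited delivers the number said to be required.

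**Working it through.** **Inputs from the article:** 40 per group, power .80, α = .05, loss of 15–20%, 48 recruited per group (Sample size); group-by-time interaction as the test (Tests of intervention effects); three waves (Recruitment, randomisation and allocation).

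**Assumptions, because the article gives no value:** medium means d = 0.5 (f = 0.25); two-sided test; equal correlation r between any two waves; d = 0.5 at both follow-ups and 0 at baseline.

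**1. Trying to reproduce 40 per group: unadjusted comparison.**
n = 2(1.960 + 0.842)² / 0.5² = 62.8, so 63 per group, or 64 with the t distribution.
Power at n = 40: noncentrality 0.5 × √(40/2) = 2.236 on 78 df gives 0.598 two-sided and 0.716 one-sided. With all 48 per group retained it is 0.679 and 0.784.
Difference detectable with 80% power, two-sided: d = 0.63 at 40 or 41 per group, 0.65 at 38.
The figure of 40 does not reproduce.

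**2. Repeated-measures conventions with f = 0.25, three waves.**
- Group-by-time interaction scaled to within-person error: λ = N × 3 × 0.0625 / (1 − r). At r = 0.5, N = 28 in total suffices (λ = 10.5). On this reading 40 per group is far more than required.
- Between-group main effect averaged over all waves: λ = N × 3 × 0.0625 / (1 + 2r). At r = 0.4, N = 78 in total (λ = 8.1), close to 80. But this is not the planned test, and it averages in a baseline at which randomised groups do not differ in expectation. A mean difference of 0.5 over three waves then requires (0 + x + x)/3 = 0.5, so x = 0.75 at each follow-up.

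**3. The planned test: 2-df interaction, d = 0.5 at both follow-ups.**
λ = (n/2) × (0.25 × 2/3) / (1 − r) = n / [12(1 − r)], on 2 and 2(2n − 2) df. For n = 40, λ = 3.33 / (1 − r):

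| r | 0.4 | 0.5 | 0.6 | 0.65 | 0.7 |
|---|---|---|---|---|---|
| λ | 5.56 | 6.67 | 8.33 | 9.52 | 11.11 |
| Power | 0.54 | 0.62 | 0.73 | 0.79 | 0.85 |

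Power reaches 0.80 at r of about 0.66. A more conservative denominator df (78) gives 0.53–0.84 over r = 0.4–0.7.

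**4. An alternative contrast on the same data: mean of weeks 4 and 12, adjusted for baseline.**
Residual variance v = (1 + r)/2 − r²; noncentrality = (0.5/√v) × √(38/2), at 38 per group:

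| r | 0.4 | 0.5 | 0.6 |
|---|---|---|---|
| v | 0.54 | 0.50 | 0.44 |
| Noncentrality | 2.97 | 3.08 | 3.29 |
| Power | 0.83 | 0.86 | 0.90 |

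**5. Dropout allowance.**
48 × 0.85 = 40.8, which meets 40. 48 × 0.80 = 38.4, which does not. Loss tolerated: 1 − 40/48 = 16.7%. Number needed at 20%: 40/0.80 = 50. The figure of 48 equals 40 × 1.2, the multiplication shortcut at 20%, and also 40/0.85 = 47.1 rounded up at 15%. On the unadjusted test, going from 40 to 38 per group lowers power from 0.60 to 0.58.

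**The case against.** The strongest reply is that the figure of about 60% belongs to an unadjusted, single-time-point test that the protocol does not plan. A repeated-measures analysis gains from within-person correlation: the planned interaction passes 80% at r near 0.66, and a baseline-adjusted comparison at one follow-up does so at r of about 0.61. Total sizes near 80 also arise under one repeated-measures convention, and the source cited for the figure cannot be seen here. All of this stands. A reader might infer that the trial has only 60% power and a 40% chance of missing a medium effect; the documents do not support that. They support only that the stated inputs do not yield .80 and that the planned test needs a correlation nobody has stated.

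On dropout, the range is approximate, its lower part is covered, the gap at 20% is about two people per arm, and a mixed model can use partial data from those who leave. This also stands, so the point is minor.

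A reader might also infer a familywise error problem from four outcomes tested at .05: 1 − 0.95⁴ = 18.5% if they were independent. That figure applies only if success on any one outcome suffices. The article states no such rule, words its first hypothesis jointly, and calls the trial exploratory. It is not part of this finding.

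The exploratory label does not remove the main point. The Sample size section makes a definite power claim, and the Discussion speaks of establishing efficacy.

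**Conclusion.** The point holds in limited form. With d = 0.5 and a two-sided .05 test, 40 per group gives about 60% power for an unadjusted comparison (64 needed, detectable d about 0.63). It gives about 54–85% for the planned interaction over r = 0.4–0.7, with 80% reached only at about 0.66. The .80 is therefore unsupported as written, but it is not shown to be unattainable. The loss allowance fails only above 16.7%, by about two per arm and two power points at 20%.

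These results rest on reading medium as d = 0.5, on equal correlations between waves, and on an effect of the same size at weeks 4 and 12; a fading effect would lower the power of the interaction and of the averaged contrast. This is a correction to make in the sample-size statement, not a defect that invalidates the design.

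**What to change.** Rewrite the sample-size paragraph in one of two ways; neither changes enrolment.

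1. Keep the claim general: 48 per group, leaving 38–41 after 15–20% loss, gives 80% power for d of about 0.63–0.65 in an unadjusted two-sided comparison.
2. Attach the .80 to one named outcome, for example the SCS-SF total, and to one contrast, the baseline-adjusted mean of weeks 4 and 12. Then 38 per group gives 83–90% power for d = 0.5 at an assumed correlation of 0.4–0.6. State that correlation and the assumption of equal effects at both visits, and name the contrast in the analysis section so that the power and the test match.

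Under either option, state the effect metric and sidedness, and say that 48 per group keeps 40 evaluable with up to 16.7% loss.

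The cost is a paragraph of text. Option 1 makes the advertised sensitivity less favourable. Option 2 commits the team to a single primary outcome and contrast, using data already due to be collected.
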